## Abstract

**Background:**

Asian patients undergoing kidney transplantation (KT) generally have better renal allograft survival and a lower burden of cardiovascular disease than those of other racial groups. The KNOW-KT aims to explore allograft survival rate, cardiovascular events, and metabolic profiles and to elucidate the risk factors in Korean KT patients.

**Methods:**

KNOW-KT is a multicenter, observational cohort study encompassing 8 transplant centers in the Republic of Korea. KNOW-KT will enroll 1,000 KT recipients between 2012 and 2015 and follow them up to 9 years. At the time of KT and at pre-specified intervals, clinical information, laboratory test results, and functional and imaging studies on cardiovascular disease and metabolic complications will be recorded. Comorbid status will be assessed by the age-adjusted Charlson co-morbidity index. Medication adherence and information on quality of life (QoL) will be monitored periodically. The QoL will be assessed by the Kidney Disease Quality of Life Short Form. Donors will include both living donors and deceased donors whose status will be assessed by the Kidney Donor Risk Index. Primary endpoints include graft loss and patient mortality. Secondary endpoints include renal functional deterioration (a decrease in eGFR to <30 mL/min/1.73 m^2^), acute rejection, cardiovascular event, albuminuria, new-onset diabetes after transplant, and QoL. Data on other adverse outcomes including episodes of infection, malignancy, recurrence of original renal disease, fracture, and hospitalization will also be collected. A bio-bank has been established for the acquisition of DNA, RNA, and protein from serum and urine samples of recipients at regular intervals. Bio-samples from donors will also be collected at the time of KT. KNOW-KT was registered in an international clinical trial registry (NCT02042963 at http://www.clinicaltrials.gov) on January 20^th^, 2014.

**Conclusion:**

The KNOW-KT, the first large-scale cohort study in Asian KT patients, is expected to represent the Asian KT population and provide information on their natural course, complications, and risk factors for complications.

## Background

The number of end stage renal disease (ESRD) patients has been increasing worldwide. In ESRD patients, the benefits in relation to survival and quality of life are greater with kidney transplantation (KT) than with dialysis. As the acute rejection rate is currently decreasing, long-term complications have become an important issue in KT patients. However, the incidence and patterns of complications in Asian KT patients may be different from those in Western countries. For example, a prospective cohort study for Chinese general population [1] and a retrospective study for Korean transplant patients [2] reported a lower incidence of ischemic heart disease than that reported in Western countries. Therefore, it is necessary to analyze outcomes and complications in KT patients in Asian countries.

The number of KTs has been increasing in Korea, and the incidence and prevalence are 33.5 and 272.3 per million people, respectively [3]. Outcomes of KT in Korea are very good in both graft and patient survival rates. Furthermore, deceased donor (DD) KT program is the most active in Korea among Asian countries with the establishment of donor action programs, and the proportion of DDKTs reached approximately 43.1% in 2012. In this sense, a systemic analysis of Korean transplant data could be valuable as representative data of the Asian population.

After transplantation, renal function tends to decrease with time. More than 60% of KT patients have an estimated glomerular filtration rate (eGFR) less than 60 mL/min/1.73 m^2^ at 1 year after transplantation, and a mild degree of proteinuria or hematuria is commonly seen in KT patients [4]. Therefore, more than 90% of KT patients are indeed chronic kidney disease patients [5]. KT patients have various complications that are derived from chronic immunosuppression or chronic kidney disease status. Cardiovascular events, malignancy, infection, and chronic rejection are the main cause of mortality or allograft failure in KT patients, and the patients also suffer from metabolic and psychosocial complications and mineral bone disorder. Analysis of the incidence and risk factors for these complications is necessary to control complications and improve transplant outcomes.

Several prospective, observational cohort studies have been performed in the Europe and North America [6-9]; however, well-designed studies in other regions are lacking. The KoreaN cohort study for Outcome in patients With KT: A 9-year Longitudinal cohort study of the Korean adult KT patients (KNOW-KT), funded by Korea Center for Disease Control and Prevention (KCDC), was launched in 2012 by a group of nephrologists, surgeons, epidemiologists, and biostatisticians in Korea. We aimed to establish an adult KT cohort; to investigate the renal allograft outcomes, mortality, and complications; to explore traditional or nontraditional risk factors for morbidity and mortality; and to establish bio-bank to integrate clinical and biological information. Here, we report the design and methodology of the KNOW-KT.

## Methods

### Organization

The KNOW-KT is being conducted in eight university-affiliated Korean transplant centers (four in Seoul City, one in Incheon city, one in Chonbuk Province, and two in Kyoungbuk Province), and involves a team of epidemiologic experts and a bio-bank in the KCDC. Epidemiologists and biostatisticians in the Medical Research Collaborating Center of Seoul National University Hospital (MRCC) are responsible for data management and statistical analysis. The KNOW-KT runs the steering committee to guide the study. The study is supervised by the Chronic Kidney Disease Advisory Committee composed by the members of the KCDC and the Korean Society of Nephrology.

### Study objectives

The primary objective of the present study is to delineate the predictors of graft failure, patient mortality, and cardiovascular and metabolic complications after KT. The secondary objective is to describe various aspects of other complications based on prospectively collected data.

### Study design and study population

This is a prospective, observational cohort study. Total enrollment population will be 1,000 adult KT recipients and their corresponding donors. Study recruitment will be performed over 4 years from 2012 to 2015. The study population will be followed up for 9 years or until their death, graft failure, or drop out. Study inclusion and exclusion criteria are shown in Table 1. Participating subjects will visit each center according to the follow-up schedule. At each visit, the subjects will undergo scheduled tests and be reviewed by the investigators for recent medical history and event occurrence. Efforts will be made in order to prevent drop-outs, i.e., providing free medical tests, frequent telephone calls and dietary education.

**Table 1 T1:** Inclusion and exclusion criteria of the KNOW-KT

**Inclusion criteria**	**Exclusion criteria**
Kidney transplant recipients and donors	Simultaneous multiple organ transplantation
Age > 18, both donors and recipients	En-bloc KT recipients
Agreed to participate and sign the consent form	Comorbidities of liver cirrhosis or interstitial lung disease at the time of transplant

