
Complication events will be collected annually as an event-based report including the date in which complication occurred. Follow-up examinations are scheduled once a year. Evaluation schedule of the KNOW-KT at each visit (Table 2) summarized details regarding the schedules for study visits, tests, and questionnaires. Immunosuppressive medications at discharge will be recorded as a baseline, and then they will be recorded annually. Medication adherence will be monitored annually using Health Questionnaires.

**Table 2 T2:** Evaluation schedule of the KNOW-KT at each visit

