### Study outcomes

Primary endpoints include graft loss and patient mortality. Graft loss is defined as requiring maintenance dialysis for more than 3 months or re-transplantation. The cause of graft loss will be pursued. Patient mortality will be classified into cardiac, noncardiac, and unknown death. Subjects who drop out from the study will be traced for this information with the help of National Health Insurance Cooperation and Korea Statistical Information Service.

Secondary endpoints include renal functional deterioration, acute rejection, cardiovascular event, albuminuria, new-onset diabetes after transplant, and QoL. Renal functional deterioration is defined as a decrease in eGFR to less than 30 mL/min/1.73 m^2^ after transplantation. Serum creatinine will be measured by an isotope-dilution mass spectrometry (IDMS)-traceable method. Estimations for defining renal deterioration will be based on both the four-variable Modification of Diet in Renal Disease formula [13], and Chronic Kidney Disease Epidemiology Collaboration creatinine equation [14]. Cardiovascular events include myocardial infarction, coronary revascularization, stroke and new onset or aggravation of congestive heart failure.

Data on other adverse outcomes including episodes of infection, malignancy, recurrence of original renal disease, fracture, chronic liver disease, and hospitalization will also be collected.

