### Statistical considerations

Descriptive analysis will be performed for baseline data. Normally distributed continuous variables will be presented as mean ± standard deviation. For nonparametric continuous variables, median with interquartile ranges will be used as the summarizing values. Categorical data will be presented with numbers and proportions. Comparison of continuous variables will be conducted with t-test or Wilcoxon rank-sum test, and categorical variables will be compared using chi-squared test or Fisher’s exact test as appropriate.

Survival time of grafts or patients, time to cardiovascular outcomes (myocardial infarction, ischemic stroke, etc.) and renal outcomes (graft loss, renal functional deterioration, acute rejection, etc.) will be estimated using Kaplan-Meier curves. Cox proportional hazard models will be used for comparison for the incidence of those outcomes among groups with and without each risk factor. However, patient death is a competing cause of renal outcomes or cardiovascular outcomes. Therefore, we will adopt competing risk models in evaluating the contributions of risk factors for those outcomes. For time-varying covariates that break the proportional hazard assumption, an extended Cox model to compare the risk of outcomes will be used.

Since more than 60% of KT patients have CKD at 1 year after transplantation [4], and CKD patients often have a non-linear eGFR decline or a prolonged period of non-progression [15], the pattern of renal functional deterioration will be explored using the Bayesian smoothing technique [16]. We will compare eGFR decline in serial measurements using a mixed linear model considering the longitudinal nature of our data. The generalized estimating equation will be used for estimating the slope of the eGFR in the area of steady and linear eGFR decline.

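### Follow-up ends at graft failure and record tracing is stated only for drop-outs, so as written deaths and cardiovascular events after graft loss are not captured

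*Protocol article*

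**What the plan says.** Under Study design and study population, the article fixes the end of observation: "The study population will be followed up for 9 years or until their death, graft failure, or drop out". Graft failure and drop-out are separate items in that list.

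Under Study outcomes: "Primary endpoints include graft loss and patient mortality". The same section gives the definition: "Graft loss is defined as requiring maintenance dialysis for more than 3 months or re-transplantation". A recipient who meets it is alive and still at risk of death. On tracing it says: "Subjects who drop out from the study will be traced for this information with the help of National Health Insurance Cooperation" (a national statistics service is named as well). In context, the information meant is graft loss and mortality.

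Under Study objectives, the primary aim is to "delineate the predictors of graft failure, patient mortality, and cardiovascular and metabolic complications after KT". Nothing limits this to the time when the graft works.

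Under Collection of data: "Complication events will be collected annually as an event-based report including the date in which complication occurred". Cardiovascular events therefore come from reports made while the patient is in follow-up.

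Statistical considerations applies Kaplan-Meier curves and Cox models to patient survival and to cardiovascular outcomes. Death is the only competing event it names.

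**The concern.** One primary endpoint ends observation of the other. A patient who returns to dialysis or is re-transplanted has reached graft loss and leaves follow-up, and no stated route collects a later death or cardiovascular event.

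Censoring at graft loss is harmless for patient mortality only if those who lose the graft have the same later risk of death as those who keep it. The Background section says that the survival benefit is greater with transplantation than with dialysis, so by the article's own premise the two groups differ.

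Two things are at stake. Reported mortality would be too low. And in a study of risk factors, the part of a factor's effect on death that acts through graft loss would be missed.

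**Working it through.** **Figures in the plan.** The article gives no figure for mortality or graft loss. Its one relevant figure concerns cardiovascular events: a detectable relative risk of 1.46 with 1,000 patients, 22% incidence at 5 years, 50% exposure, two-sided 5% alpha and 80% power. Schoenfeld's formula gives 4 × (1.960 + 0.842)² / (ln 1.46)² ≈ 220 events, and 220 / 0.22 = 1,000. The figure reproduces and is not in dispute.

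**Inputs for the size (assumptions, since the article gives none).** Constant yearly rates and a full 9 years of follow-up, T = 9:
- graft failure g = 1-3%
- death with a functioning graft m = 1-2%
- death rate after graft loss k × m, with k = 3-5

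**Formulas (three states: functioning graft, graft lost, dead).**
- Deaths with function: A = m/(g+m) × (1 − e^(−(g+m)T))
- Graft losses: L = g/(g+m) × (1 − e^(−(g+m)T))
- Alive after graft loss at T: V = g × (e^(−kmT) − e^(−(g+m)T)) / (g + m − km)
- Deaths after graft loss: B = L − V
- True mortality: A + B
- Kaplan-Meier mortality censored at graft loss: 1 − e^(−mT)

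**Worked example (g = 2%, m = 1%, k = 5).**
- e^(−0.27) = 0.7634, so A = 0.0789 and L = 0.1577.
- V = 0.02 × (0.6376 − 0.7634)/(−0.02) = 0.1258, so B = 0.0320.
- True mortality = 0.0789 + 0.0320 = 11.1%.
- Kaplan-Meier censored at graft loss = 1 − e^(−0.09) = 8.6%.
- Share of deaths after graft loss = 0.0320/0.1109 = 29%.

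**Across the assumed range.** The last column is the true 9-year mortality ratio for a factor that triples g and leaves m and k unchanged.

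| g | m | k | Deaths after graft loss | True 9-year mortality | Kaplan-Meier, censored | True ratio, g tripled |
|---|---|---|---|---|---|---|
| 1% | 1% | 3 | 11% | 9.3% | 8.6% | 1.13 |
| 1% | 2% | 3 | 11% | 17.6% | 16.5% | 1.12 |
| 2% | 1% | 5 | 29% | 11.1% | 8.6% | 1.37 |
| 3% | 1% | 5 | 38% | 12.2% | 8.6% | 1.45 |
| 3% | 2% | 5 | 35% | 22.4% | 16.5% | 1.40 |

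The understatement runs from 0.7 points (first row) to 5.9 points (last row).

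**Why the censored analysis shows no effect for such a factor.** The censored estimate 1 − e^(−mT) does not contain g, so both groups give the same value and a ratio of 1.0. In the worked example, tripling g to 6% raises true mortality from 11.1% to 15.2%, while the censored estimate stays at 8.6% in both groups.

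**Cardiovascular power.** If 5-10% of the 220 planned events were lost in this way (an assumption), 209-198 would remain, and power for a relative risk of 1.46 would fall from 80% to about 78-76%. The loss of power is small; the gap in what is measured matters more.

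**The case against.** **The article never says that deaths are censored at graft loss.** This is true. The end-of-follow-up sentence could mean only the end of scheduled visits, with vital status obtained from national sources, and the full protocol may say so. A reader might infer that the article openly plans to censor deaths there; it does not, and informative censoring is an inference from several sections read together. But the article does state a stopping rule and does say who is traced: "Subjects who drop out from the study will be traced for this information". If wider tracing is intended, these two sentences misdescribe it and still need correcting. Even if graft-failure exits counted as drop-outs, the tracing would not reach cardiovascular events.

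**The intended quantity may be death with a functioning graft.** A cause-specific Cox hazard for that outcome is interpretable without assuming equal risk after graft loss. But the article does not define mortality in that way, and graft loss would then be a competing event, which it does not name.

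**Risk factors acting through graft loss would not vanish.** This stands. Graft loss is the other primary endpoint, so such a factor can still be found there. What is lost is its total effect on death.

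**The upper figures rest on the harshest assumptions.** This also stands. The Background section calls Korean graft and patient survival very good. At graft failure of 1% per year the missed share is 11-17%.

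**A reader might also infer that the stopping rule makes the eGFR slope too shallow**, because the article plans this: "The generalized estimating equation will be used for estimating the slope of the eGFR in the area of steady and linear eGFR decline". The documents do not support that. Once a graft is lost its eGFR is no longer a meaningful series, so longer follow-up would not restore it. Restriction to segments of steady decline leaves out periods of non-progression and could as well steepen the slope. A mixed linear model is already planned for serial eGFR.

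**Conclusion.** The point holds for mortality and cardiovascular events. As written, the stopping rule and the limited tracing leave both unobserved after graft loss, although mortality is a primary endpoint and predictors of both are in the primary objective. The survival analyses would then estimate something closer to death with a functioning graft.

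Under the assumed rates, about 11-38% of 9-year deaths are missed, 9-year mortality is understated by about 0.7-6 percentage points, and a factor that triples graft failure without a direct effect on death has a true mortality ratio of about 1.1-1.45 but would show 1.0. The direction rests on a higher death rate after graft loss, which the Background section supports. The size rests wholly on assumed constant rates and a full 9 years of follow-up.

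Nothing here bears on the eGFR slope analysis, and the article does not itself declare that deaths are censored at graft loss.

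**What to change.** 1. In Study design and study population, make graft failure a recorded event and not the end of observation for mortality and cardiovascular outcomes.
2. In Study outcomes, extend the national insurance and statistics linkage already planned for drop-outs to recipients with failed grafts, covering vital status, cause of death and cardiovascular events to year 9. Add cardiovascular events to the tracing of drop-outs too.
3. In Statistical considerations, analyse mortality from transplantation to year 9 without censoring at graft loss, with graft failure as a time-dependent (intermediate) state. The total effect of a risk factor should come from a model that does not adjust for graft failure; the state model then shows how much of it passes through graft loss.
4. Report death with a functioning graft separately, with graft loss as a competing event.

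The cost is a modest extension of the linkage and of its consent and approval wording, with no extra visits. Study status reports 535 of 1,000 patients enrolled, so the new wording can be in place for the remaining recruits; patients already enrolled may need their consent checked for linkage after graft failure.

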### Collection of data

Baseline data will be collected during the pre-transplant screening period, which include socio-demographic information (age, sex, smoking history, history of alcohol drinking), information on quality of life (QoL), socio-economic status, educational level, physical activity, health behaviors, and health care facility utilization. Comorbid status will be assessed by the age-adjusted Charlson co-morbidity index [10]. The QoL will be assessed by the Kidney Disease Quality of Life Short Form (KDQoL-SF) [11]. The KDQoL-SF consists of generic core (physical component summary and mental component summary) and kidney disease-targeted domains (symptoms/problems, burden of kidney disease, and effects of kidney disease). Generic core represents the physical and mental aspects of QoL, and kidney disease-targeted domains focus on disease-related concerns. At the time of KT, the following clinical parameters will be collected; (1) general information about transplant (date of transplantation, number of transplant experience, donor-recipient relationship and desensitization) (2) recipient information (date of birth, sex, cause of ESRD, comorbidities such as diabetes mellitus and hypertension, history of malignancy, history of cardiovascular diseases, and medications including immunosuppressant) (3) donor information (date of birth, sex, body weight, height, comorbidities such as hypertension, history of malignancy). Donors include both living donors and DDs. DDs include brain death donors of standard and expanded criteria, and donation after cardiac death. The quality of DD kidneys will be assessed by the Kidney Donor Risk Index [12]. Physical examination including anthropometric measurements (height, weight, waist-to-hip ratios) and measurements of the resting office blood pressure and pulse pressure will be conducted. Laboratory tests include serum levels of calcium, phosphorus, parathyroid hormone, total cholesterol, high-density lipoprotein cholesterol, triglycerides, low-density lipoprotein cholesterol (calculated), hemoglobin, glycated hemoglobin, and C-reactive protein. Immunologic evaluation includes human leukocyte antigen (HLA) typing, performing HLA crossmatch (complement-dependent cytotoxicity-based method and flow cytometry-based method), and measuring panel reactive antibody levels. Pre-transplant echocardiography, measurement of pulse-wave velocity and ankle brachial index, and coronary calcium computed tomography will be performed as cardiac evaluations.

Complication events will be collected annually as an event-based report including the date in which complication occurred. Follow-up examinations are scheduled once a year. Evaluation schedule of the KNOW-KT at each visit (Table 2) summarized details regarding the schedules for study visits, tests, and questionnaires. Immunosuppressive medications at discharge will be recorded as a baseline, and then they will be recorded annually. Medication adherence will be monitored annually using Health Questionnaires.

**Table 2 T2:** Evaluation schedule of the KNOW-KT at each visit

	**Visit***										
Parameter	Screening	Baseline	1	2	3	4	5	6	7	8	9
Informed consent	O										
Medical History	O										
Eligibility confirmation	O										
Recent events			O	O	O	O	O	O	O	O	O
Medications		O	O	O	O	O	O	O	O	O	O
Health Questionnaires		O	O	O	O	O	O	O	O	O	O
KDQOL questionnaires		O		O		O		O		O	
Blood pressure		O	O	O	O	O	O	O	O	O	O
Anthropometry		O	O	O	O	O	O	O	O	O	O
CBC, chemistry		O	O	O	O	O	O	O	O	O	O
IDMS-serum Cr, eGFR		O	O	O	O	O	O	O	O	O	O
Cystatin C		O	O	O	O	O	O	O	O	O	O
HbA1c (diabetic subjects)		O	O	O	O	O	O	O	O	O	O
Lipid, CRP, iron profile		O	O	O	O	O	O	O	O	O	O
Intact PTH, vitamin D^1^		O	O	O	O	O	O	O	O	O	O
Urinalysis		O	O	O	O	O	O	O	O	O	O
Urine protein/creatinine		O	O	O	O	O	O	O	O	O	O
EKG, chest X ray		O	O	O	O	O	O	O	O	O	O
Serum BK real time PCR			O				O				
PRA I & II		O	O				O				
HLA crossmatch		O									
HLA typing		O									
Viral serology^2^		O									
LS spine Lateral X-ray for vascular calcification		O	O	O	O	O	O	O	O	O	O
Pulse wave velocity, Ankle-brachial index		O			O			O			
Echocardiography		O			O			O			
MDCT for coronary calcium score		O						O			
Bone mineral density		O			O			O			
DNA sample*		O									
Serum/urine sample		O	O		O		O				
RNA sample			O		O		O				

CBC, complete blood count; CMV, cytomegalovirus; CRP, C-reactive protein; HLA, human leukocyte antigen; IDMS-serum cr, serum creatinine measurement using IDMS-traceable method; KDQOL, Kidney Disease Quality of Life; MDCT, multidetector computed tomography; PRA, panel reactive antibody; PTH, parathyroid hormone. ^1^25-hydroxy- and 1,25-dihyroxy-vitamin D. ^2^HBsAg, anti-HBs, anti-HCV, and anti-CMV IgG.

All the reported data will be collected in a predefined case report format and subsequently entered into a web-based electronic data-warehouse. The electronic data input and management system for the KNOW-KT was developed by the data management division in the MRCC.

